### Participant timeline

The participant timeline is presented in Table 1.

**Table 1 Tab1:** Participant schedule of events

Assessment	Remote screening assessment day 14	Study time point					
		Baseline assessment day 1 (remotely)	IIET visit (within 7 days of Baseline visit)	Follow up telephone call — IE arm only (within 7 days of IIET visit)	Assessment 2 day 28–33 (remotely)	Assessment 3 month 3 (± 7 days) (remotely)	Assessment 4 month 6 (± 7 days) (remotely)
Medical history	X	X					
Concomitant medication	X	X		X	X	X	X
Consent	X						
Observed blood pressure and heart rate		X			X	X	X
IE ability test	X						
Incremental IE test and IE programme provided (for those randomised to intervention arm only)			X				
AE review				X	X	X	X
Diet questionnaire		X			X	X	X
Exercise questionnaire		X			X	X	X
Quality of life questionnaire		X			X	X	X
Collection of IE exercise diary (for those randomised to intervention arm only)				X	X	X	X
Collection of home blood pressure and heart rate readings	X (between day 7 and day 1)	X		X	X	X	X
Health resource use questionnaire					X	X	X
IE experience questionnaire					X		

### Sample size

Review of current literature revealed few IE studies in a hypertensive population. These studies were small (*n* < 25), conducted under different conditions to the proposed study, and showed low precision and large variability in estimates of the standard deviation (SD). A sample size of 100 participants, 50 per arm, will be used in the study. Allowing for 20% attrition and 6.5% incomplete data, 74 participants (37 in each arm) will have completed change measures at 4 weeks. This is in line with the recommended sample size of 70 to estimate key parameters from external pilot RCTs [62]. A sample size of 74 produces a two-sided 95% confidence interval with a width of 1.33 when the standard deviation is 4. This estimate of 4 has been taken from a previous study (*N* = 24) [10]. The sample size confidence interval has been calculated using Pass11 software (PASS 11. NCSS, LLC. Kaysville, UT, USA, www.ncss.com).

### Recruitment

Participants will be identified opportunistically through patient database searches and invited to participate. The study will also be advertised with ethically approved advertising materials, in participating GP practices, with electronic adverts on their websites, social media and newsletters as well as by text message to potential participants.

## Assignment of interventions: allocation

### Sequence generation

Random permuted blocks will be used within stratification (of site and age), ensuring that treatments are balanced at the end of every strata block. There are two stratification groups for age; these are age 18–49 years and ≥ 50 years. It is anticipated that between two to six primary care sites in South East England will be included in the study.

### Concealment mechanism

Participants will be allocated to either the control or isometric exercise arm using a third-party supplier of randomisation services [63]. This internet-based service allows investigators to randomise patients from anywhere in the world through a web browser.

### Implementation

The investigators will implement the allocation created by the online randomisation software [63].

## Assignment of interventions: blinding

This feasibility study was intended to replicate real life NHS practice where patients would be fully aware of any medical intervention prescribed by their healthcare professional. Therefore, the healthcare professionals (delivering the exercise intervention) and the participants/patients (performing the exercise) were not blinded to the allocated lifestyle intervention arms.

### Data collection and management

#### Plans for assessment and collection of outcomes

The success of intervention delivery by healthcare professionals in a primary NHS healthcare settings will be determined using both qualitative data (*remote*) and the heart rate data recorded by the participants at the end of each isometric wall squat bout x4 per session over the 3 sessions completed in the first week using a wireless heart rate monitor and chest strap (Sigma PC 15.11, Neustadt/Weinstraße, Germany). The average HR calculated from the first 3 sessions will then be compared against the individuals’ target training HR (calculated as 95% of HR_peak_ measured during the individuals incremental isometric exercise test IIET) with an acceptable target heart rate range (THRR) of 76–111% of heart rate peak [60]. Perceptions of intervention delivery by healthcare professionals will be explored in qualitative focus groups (*remote*). The focus group questions for both healthcare professionals and participants were guided by the work of O’Cathain et al. [64] on the use of qualitative research in feasibility studies for randomised controlled trials. The groups will discuss the intervention content and delivery and the trial design, conduct and processes. For professionals, the core questions will be the following: What are your views on how the isometric exercise was implemented? Is the study design acceptable? How did the planned recruitment practices work in practice? Are the proposed process and outcome measures valid for this group of service users?

Any change in BP following the IE intervention will be determined using the *home blood pressure data* (measured using an automated upper arm blood pressure monitor [Omron M3 Intellisense, Kyoto, Japan] at weeks 4, 12, and 24) recorded in the participants diaries and comparing this against their *observed* baseline (recorded at day 1). This data will also be used to estimate BP variance by calculating systolic BP change from baseline at each endpoint. An estimate of the difference in change from baseline between the isometric exercise and control group will be calculated with 80% and 95% confidence intervals.

Accuracy of IE protocol delivery will be determined using data from three fidelity assessments; the first being healthcare professional competency checks administered during their isometric exercise prescription training; the second being expert observation/evaluation of at least the first IIET delivered by each HCP; and then finally, by third party examination of the first week of heart rate data recorded in the study diaries of each HCP’s specific participants, with average HR calculated from the first 3 sessions being compared against the individuals target training HR as described above.

Execution of the IE training protocol in the home will be assessed for each individual participant at the end of the first week by checking to see if their mean training heart rate per week falls within target heart rate range/reference interval (76–111%) *data for weeks 4, 12 and 24 will now be assessed at the end of the 6-month training period*. An estimate of the short- (4 week) and medium-term (3 and 6 month) adherence rates to IE training will be based upon the data collected from participant diaries to calculate the proportion of participants completing ≥ two thirds of all IE sessions (12, 36 and 72) at each time point respectively. Patient recruitment and participant attrition rates will be calculated based upon the average number of participants recruited per week over the 7 month recruitment period and the number of withdrawals from the study once the last follow-up call to the last participant has been made.

Participant experiences of IE will be assessed through a quantitative online survey conducted at week 4. All participants receiving the IE intervention will be invited to take part in one of two focus groups (*remote*) to draw out respondents’ attitudes, feelings, beliefs, and experiences regarding the intervention [65]. The core focus group questions for participants were also directed by the guidelines for using qualitative research in feasibility studies [64]. What are your views on how you applied the isometric exercise intervention? What are your thoughts on how the study was conducted? What do you think are important outcomes to consider in a full trial? *This will also be used as an opportunity to explore possible negative effects of COVID-19 on recruitment rates and participation*. These groups will be held at month 4 and month 8 of the recruitment period with 6–8 participants in each group. One focus group will also be undertaken with healthcare professionals involved in the intervention delivery at the end of the recruitment period to explore views and experiences of the IE intervention. Lay and professional members of the research team will co-produce the topic guide and co-facilitate the focus groups. The focus groups are proposed to last for between 60 and 90 min. The groups will be digitally recorded and transcribed. Telephone interviews (*n* = 5–10) will be conducted with stakeholders from GP practices which are not recruitment sites and not involved in the intervention delivery to explore the willingness of GPs and primary care healthcare professionals to consider IE as a viable treatment option for patients, including barriers and facilitators for delivering and integrating this within an NHS care pathway for hypertension.

The economic evaluation of delivering the IE intervention will be calculated once the last follow-up call has been made to the last participant and will be estimated from Healthcare resource use data and quality-adjusted life years (QALYs). Since QALYs are the primary outcome of the economic evaluation, utility values will be obtained from patients’ responses to each of the EQ-5D-5L at the beginning of the intervention and at week 4 and months 3 and 6 after the intervention [66, 67].

New insight into the accuracy of home BP measurements to monitor changes in BP will be based upon the BP data (observed and home readings) recorded (at baseline assessment, day 1; assessment 2, week 4; assessment 3, month 3; and assessment 4, month 6) in the participant diaries, along with expert evaluation of the participants ability to carry out the measure.

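### Systolic BP change, and the variance estimate built on it, subtracts a supervised day 1 reading from self-recorded diary readings, so its SD fits neither like-for-like endpoint

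*Protocol article*

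**What the plan says.** Under Plans for assessment and collection of outcomes, the protocol article defines BP change directly: "Any change in BP following the IE intervention will be determined using the *home blood pressure data", taken at weeks 4, 12 and 24, "recorded in the participants diaries and comparing this against their *observed* baseline (recorded at day 1"). The next sentence links this to the variance: "This data will also be used to estimate BP variance by calculating systolic BP change from baseline at each endpoint". The Objectives make the variance of BP change a primary objective, because it is to size the definitive trial.

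Table 1 lists the two kinds of reading in separate rows. "Observed blood pressure and heart rate" is scheduled at day 1, day 28–33, month 3 and month 6. "Collection of home blood pressure and heart rate readings" is scheduled at those same points, at the first-week call in the exercise arm, and in the screening column as "X (between day 7 and day 1"). The closing paragraph on outcome collection says that the accuracy of home measurement will be judged from "BP data (observed and home readings) recorded (at baseline assessment, day 1; assessment 2, week 4; assessment 3, month 3; and assessment 4, month 6").

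The Outcomes list and the Statistical methods section refer only to participant BP data and to baseline values. They do not alter the definition of change.

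**The concern.** The plan treats observed and home readings as two measures whose agreement is under study, then subtracts one from the other in a primary outcome. Both types are scheduled at both ends of the change, so a like-for-like change is available in either form.

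Two things are at stake.

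- **The SD.** It reflects the error of one observed occasion at baseline, the error of the diary readings at follow-up, and any person-to-person variation in the gap between the two. A definitive trial that uses one measure throughout would have a different SD.
- **The within-arm change.** The Discussion makes part of the viability judgement depend on resting BP falling or staying the same after the intervention. Any systematic gap between observed and diary readings enters that quantity in full.

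**Working it through.** **1. The plan's own figure.** The Sample size section gives n = 74, SD 4, two-sided 95% and width 1.33. The exact interval for one SD with 73 degrees of freedom uses chi-square quantiles 51.26 and 98.52:

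- lower limit 4 × √(73/98.52) = 3.443
- upper limit 4 × √(73/51.26) = 4.773
- width 1.330

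The figure reproduces. It takes the SD as given, so the choice of measure does not affect it.

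**2. Inputs for the effect on the variance.** The documents give no error SDs for either type of reading. All of these are assumptions:

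- between-person SD τ = 8 mmHg, so τ² = 64 and τ⁴ = 4096
- home reading error SD h = 3 or 4
- observed reading error SD o from equal to h up to 8
- SD of true individual response d = 0 to 4
- independent errors

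**3. Formulas.**

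- Raw change variance: home-home 2h² + d²; mixed o² + h² + d²; observed-observed 2o² + d².
- ANCOVA residual variance, follow-up error f, baseline error b: τ² + f² + d² − τ⁴/(τ² + b²). Home-home has f = b = h, mixed has f = h and b = o, observed-observed has f = b = o.

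The ANCOVA residual is the relevant quantity for sample size, because Statistical methods specifies ANCOVA adjusted for baseline for the definitive trial.

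**4. Results.**

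| h | o | d | Raw change variance: home-home / mixed | Ratio | ANCOVA residual: home-home / mixed | Ratio |
|---|---|---|---|---|---|---|
| 3 | 3 | 0 | 18 / 18 | 1.00 | 16.9 / 16.9 | 1.00 |
| 3 | 4 | 4 | 34 / 41 | 1.21 | 32.9 / 37.8 | 1.15 |
| 3 | 4 | 0 | 18 / 25 | 1.39 | 16.9 / 21.8 | 1.29 |
| 4 | 6 | 4 | 48 / 68 | 1.42 | 44.8 / 55.0 | 1.23 |
| 3 | 6 | 0 | 18 / 45 | 2.50 | 16.9 / 32.0 | 1.90 |
| 3 | 8 | 0 | 18 / 73 | 4.06 | 16.9 / 41.0 | 2.43 |

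Worked example, last row: home-home 64 + 9 − 4096/73 = 16.9; mixed 64 + 9 − 4096/128 = 41.0; ratio 2.43.

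**5. Direction.** With h = 3, o = 6 and d = 0, the SD of raw change is √18 = 4.24 home-home, √45 = 6.71 mixed and √72 = 8.49 observed-observed. The ANCOVA residuals are 16.9, 32.0 and 64 + 36 − 4096/100 = 59.0. The mixed value lies between the other two. It overstates the variance for a home-based definitive trial and understates it for an observed-based one.

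**6. Offset.** A constant observed-minus-home gap shifts every change by the same amount. It therefore leaves the SD and the between-arm contrast unchanged and moves only the within-arm means. A gap that varies between people adds its own variance to the mixed change.

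**The case against.** The best reply is that the two measures are close. "Observed" here does not mean a clinic reading. The Objectives and secondary outcomes speak of observed home readings, the baseline assessment is remote, and the Discussion contrasts observed home readings with clinic ones. The comparison is therefore supervised against unsupervised measurement at home. The article does not give the number of readings in an observed session, and it does not say that follow-up home readings are averaged. Averaging is mentioned only for the white-coat exclusion, although the reminder to start taking home BP suggests repeated readings. With equal errors and no person-specific gap, the ratio is 1.0. This stands, and it limits how large a claim can be made.

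A second reply is that no data are lost, since both types are collected and either change could be derived at analysis. That makes the correction cheap, but the stated definition still points to the mixed change.

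A third is that a separate day 1 baseline avoids the screening readings. The Exclusion criteria remove averaged home systolic BP below 135 mmHg, apparently using the home readings taken between day 7 and day 1. Putting those into the baseline would add regression to the mean to within-arm change. The article does not offer this as its reason, but the point is sound and bears on the fix.

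A reader might go further and infer that the SD would be about 8.5 instead of 4.2 and the definitive trial some four times too large. The documents do not support that. Those values (√73 = 8.54 against √18 = 4.24) come from the extreme corner of the assumptions and use raw change, whereas the stated model is ANCOVA.

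**Conclusion.** The point holds in limited form. As written, the plan estimates the variance of a mixed change, and that SD is not the SD of either endpoint a definitive trial would use if it kept to one measure. Neither size nor direction can be derived from the documents. On the assumptions shown, the ANCOVA residual variance is between 1.0 and about 2.4 times the home-home value, and sample size scales with it if the definitive trial uses home readings throughout. If that trial uses observed readings throughout and they carry more error, the mixed estimate is too small.

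The within-arm change takes the full systematic offset, which matters for the viability judgement in the Discussion. A reader might also infer that the treatment comparison is biased. It is not biased by a constant offset, which cancels between randomised arms. What remains is lost precision if the observed baseline is the noisier covariate.

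**What to change.** State in the outcome definition that change uses the same measurement type at baseline and follow-up, and name the type intended for the definitive trial. Use that type's baseline as the ANCOVA covariate. Report the SD of the other like-for-like change as a sensitivity analysis.

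If home-home is chosen, take the day 1 home readings as baseline, or report results with and without the day 7 to day 1 screening readings, because those appear to feed the exclusion below 135 mmHg.

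The cost is one sentence and one additional analysis. Table 1 already schedules every reading needed, and the sample size justification needs no change.

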#### Plans to promote participant retention and complete follow-up

Participant adherence will be measured as outcome data including the number of IE sessions completed. Completion of at least 8 of 12 sessions between baseline and the 4 week timepoint will be deemed adherence to the intervention. The percentage of completed IE sessions that meet the required target HR threshold will be calculated. The percentage of participants that deviate from protocol will be recorded to assess fidelity to the IE programme. The rate of healthcare professionals that pass the competency assessment after the half-day training session will be calculated.

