**Fig. 4 Fig4:**
[figure not shown]
Bend and Squat device used to determine knee joint angle during wall squat exercise

Once the device is set to the participants personal wall and floor measurements necessary to replicate the angle required to elicit 95% HR_peak_, they will then be asked to squat in this set position as a fidelity check to ensure that it equates to their specific training knee joint angle. In the unlikely event that it is necessary, a slight adjustment to the wall height can be used to achieve the correct knee joint angle prescribed. Before the client leaves the surgery to commence their training, it will be ensured that they are completely confident with the information they have received. *Participants will then given a web link (USB stick if required) containing video instructions of how to set up their HR monitor, use the Bend and Squat device to perform a IE training session and how to record the necessary training data in their diaries*. They will also be provided with the study research assistant contact telephone and e-mail helpline address for use during office hours.

All IE training sessions thereafter will be completed in the home. Participants will use their Bend and Squat device to perform an IE training session composed of 4 bouts of 2-min wall squats with 2 min recovery in between each bout [60]. Participants will be instructed to perform three IE training sessions a week, ideally on alternate days to allow for adequate between session recovery. During the IE training sessions, the HR value displayed at the end of each 4 × 2-min wall squat along with their RPE will be recorded for subsequent analysis. If the mean HR of the four exercise bouts deviates from the prescribed THRR on two consecutive sessions in the first week of IE training (acting as a fidelity check), the knee joint angle and thus their Bend and Squat set-up will be altered accordingly based upon further interpolation of their HR/knee joint angle relationship.

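### The 4-week adherence rule counts 12 sessions from baseline although training starts up to 7 days later, so its two-thirds threshold is really about 57–89% of available sessions; time origin and visit labels also conflict

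*Protocol article*

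**What the plan says.** - **4-week rule** (Plans to promote participant retention and complete follow-up): "Completion of at least 8 of 12 sessions between baseline and the 4 week timepoint will be deemed adherence to the intervention".
- **All three time points** (Plans for assessment and collection of outcomes): adherence is "the proportion of participants completing ≥ two thirds of all IE sessions (12, 36 and 72) at each time point respectively". No time origin is given there. The same section dates the home blood pressure follow-ups at weeks 4, 12 and 24.
- **Outcome list** (Outcomes, Secondary): adherence is recorded at week 4, month 3 and month 6, dated from the intervention rather than from baseline.
- **Schedule** (Participant timeline, Table 1): baseline is day 1. The programme is handed over at the "IIET visit (within 7 days of Baseline visit"). The 4-week contact is "Assessment 2 day 28–33 (remotely") and the last is "Assessment 4 month 6 (± 7 days) (remotely"); the 3-month contact has the same ± 7 day window.
- **Training** (Intervention description, text after Fig. 4): once the device has been set at the test visit, "All IE training sessions thereafter will be completed in the home", and "Participants will be instructed to perform three IE training sessions a week".

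**The concern.** A two-thirds rule should ask the same of every participant. Here the denominator is fixed, while the time available for training depends on how soon after baseline the test visit is booked and where in its window the assessment falls. Two people with the same habits can be classified differently because of appointment dates, and a site slow to arrange test visits will look less adherent.

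Adherence at 4 weeks, 3 months and 6 months is a stated secondary objective. The Statistical methods section uses adherence to inform compliance criteria for the full trial, and the Discussion makes adherence at least as good as that of other lifestyle measures part of the case for viability. With 50 participants planned in the exercise arm, and 37 per arm expected to have complete 4-week data, a few classifications driven by scheduling would move the reported proportion.

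**Working it through.** **1. Reproduce the plan's figures.** Three sessions per week × 4, 12 and 24 weeks = 12, 36 and 72. Two thirds of these = 8, 24 and 48. All agree with the protocol, so the denominators assume exactly 4, 12 and 24 full training weeks.

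**2. Sessions that fit by the 4-week assessment.** Sessions = 3 × (days from baseline to assessment − lag to test visit) / 7. With baseline as day 1, day 28 is 27 days later and day 33 is 32 days later.

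| Lag | Assessment | Training days | Sessions (rounded) | 8 as a share |
|---|---|---|---|---|
| 0 days | day 28 | 27 | 11.6 (12) | 67% |
| 0 days | day 33 | 32 | 13.7 (14) | 57% |
| 7 days | day 28 | 20 | 8.6 (9) | 89% |
| 7 days | day 33 | 25 | 10.7 (11) | 73% |

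An intermediate case: a 3-day lag and a day-28 visit leave 24 days, 3 × 24/7 = 10.3, about 10 sessions, and 8/10 = 80%.

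**3. Where the fixed cut-off departs from two thirds.** Rounded up, two thirds of 9, 10, 11, 12, 13 and 14 sessions is 6, 7, 8, 8, 9 and 10. A fixed cut-off of 8 is too high at 9 or 10 available sessions, unchanged at 11 or 12, and too low at 13 or 14.

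**4. Effect on classification.** Assume independent sessions with constant completion probability p; the protocol gives no such value. P(classed adherent) = P(X ≥ cut-off), X binomial (n, p).

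| Sessions available | Fixed cut-off 8, p = 0.75 | Fixed cut-off 8, p = 0.80 | Two-thirds cut-off, p = 0.80 |
|---|---|---|---|
| 9 | 0.30 | 0.44 | 0.91 (6 of 9) |
| 10 | 0.53 | 0.68 | 0.88 (7 of 10) |
| 11 | 0.71 | 0.84 | 0.84 (8 of 11) |
| 12 | 0.84 | 0.93 | 0.93 (8 of 12) |
| 14 | 0.96 | 0.99 | 0.87 (10 of 14) |

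At p = 0.80 the fixed rule runs from 0.44 to 0.99 across the permitted timings; the proportional rule stays between 0.84 and 0.93. What remains is whole-number rounding.

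**5. Later time points.** Take a calendar month as about 30.4 days (assumption), so month 3 is about 91 days and month 6 about 183 days.

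- Month 3, nominal date: 39.1 sessions with no lag and 36.1 with a 7-day lag; 24 is 61% and 66%. Over the ± 7 day window the range is 57–72%.
- Month 6, nominal date: 78.3 and 75.3 sessions; 48 is 61% and 64%. Over the window the range is 59–66%.
- If the visits are at weeks 12 and 24, with a 7-day lag: 3 × 11 = 33 and 3 × 23 = 69 sessions; 24/33 = 73% and 48/69 = 70%.

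Week 24 is 168 days. Calendar month 6 less 7 days is about 176 days, so the two labels for that visit do not overlap.

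**The case against.** The strongest reply is that only the 4-week sentence names baseline. The outcome list dates adherence from the intervention, and from that origin 12, 36 and 72 are exactly right and the lag vanishes. Months may also be shorthand for four-week blocks, since blood pressure follow-up is described as weeks 4, 12 and 24. Counting against the prescribed 12 sessions is itself a legitimate measure of dose received, and the number of sessions completed will be recorded in any case. The outcome is descriptive, in one arm of a feasibility study, with no numerical progression threshold attached.

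Much of this stands, and it limits the point. A reader might infer that the rule is far stricter at 4 weeks and laxer at 6 months, so that any trend in adherence is an artefact. The documents do not support that. With no lag the 4-week threshold is 57–67%, and 89% is one corner of the range. The laxer 6-month figure of 61–64% needs calendar months; under week 24 with a 7-day lag it becomes about 70%, which is stricter. The distribution of lags is not given, so neither the sign nor the average size of any shift can be stated.

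What the reply does not remove is the contradiction. The one sentence that defines adherence at 4 weeks counts from baseline, against the outcome list, and Table 1 permits a later training start. This is not detail left to a fuller document: the article fixes the numbers and the origin, and they do not fit its own schedule.

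**Conclusion.** The point holds in limited form. Followed as written, the 4-week rule applies a threshold of about 57–89% of available sessions, depending on appointment timing, in place of the intended 67%. The main harm falls on participants with only 9 or 10 sessions available, who need 80–89%; those with 13 or 14 are treated leniently. At 3 and 6 months the fixed denominators agree with the week labels but not with the calendar months in Table 1. The discrepancy at 6 months is modest, and no overall direction over time can be claimed.

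The session counts and percentages rest only on the stated frequency and visit windows, plus the 30.4-day month for the later visits. The probabilities also rest on an assumed, constant and independent completion rate. The average effect cannot be computed. This should be corrected because adherence is a stated objective that feeds the full trial's compliance criteria, but no between-arm estimate depends on it.

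**What to change.** - Use one time origin, the test visit, and one set of labels (weeks 12 and 24, or months 3 and 6) in the outcome list, Table 1, the outcome-assessment section and the retention section.
- For each participant, count sessions available as three per week from the test visit to the actual assessment date. Class as adherent at two thirds or more of that number, at all three time points, and state how fractions are rounded.
- Report the percentage of available sessions completed alongside the binary result, since it does not depend on rounding.

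The cost is wording only: the visits are scheduled and the exercise diaries are already collected. The small downside is that the measure becomes relative to available time, so a late starter can be adherent after fewer sessions. The raw count against 12, 36 and 72 can be kept as a secondary description of dose received.
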